The evidence base regarding persistent post-repair risks and consequences is underdeveloped, which limits clinical and counseling interventions capable of mitigating harmful processes. Most evaluation has been retrospective. Most previous prospective research on repair failure is limited to the fistula repair hospitalization or early clinical-follow up, with sparse data on predictors of later fistula repair breakdown and recurrence. A study in Guinea reported that women not sexually active at follow-up and those with urethral involvement, damaged bladder neck, and presence of vaginal scarring had significantly higher incidence of fistula recurrence.^14^ Self-reported precursors to fistula recurrence in this study included farm work (19%), walking (12%), sexual intercourse (10%), and pregnancy or childbirth (10%).^14^ In Ethiopia, recurrence was linked to physical strain, sexual intercourse, heavy work, or jostling during transit.^15^ Three smaller studies in Ethiopia, Malawi, and Sudan identified fistula recurrences occurring during a subsequent childbirth.^12,28,29^

Fistula recurrence can be mechanistically characterized as surgical breakdown or re-injury, thus capture of the biological and social factors important to each potential pathway is key. The literature on enhanced recovery after surgery has identified patient counseling, physical conditioning, avoidance of alcohol and smoking, and good nutrition as protective.^30^ Surgical site infection, an intermediate factor associated with late breakdown, is more common among patients with co-morbidities (particularly diabetes), advanced age, risk indices, and lengthier surgery.^31^ Factors responsible for re-injury may include the biological and social structures that increased women’s risk of developing a first fistula, including limited access to emergency obstetric care, and it is possible that a woman’s risk of fistula recurrence following surgery will be different due to the biological alterations occurring within the surgery itself, largely impacted by fistula characteristics which are likely to be important predictors of recurrence outcomes. A small Ethiopian study comparing women with and without persistent post-repair urinary incontinence found that leakage was significantly more likely among younger women at first vaginal birth.^22^

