Urinary incontinence following fistula repair is complex due to a variety of anatomic and functional factors at play which often remain uncharacterized, particularly over time.^32–34^ Research on potential intervention points for reducing persistent and incident post-repair incontinence is limited by the breadth of factors assessed, lack of differentiation between incontinence types, and lack of longitudinal follow-up. Predictors of immediate post-repair incontinence include fistula severity, including size and location, presence of vaginal scarring, and shorter urethral length.^11,16,35^ Less is known about incident incontinence following successful surgical resolution.^14,17^

To inform clinical and counseling interventions to optimize women’s health and quality of life following fistula repair, we have developed a mixed-methods research study incorporating a longitudinal cohort to robustly identify predictors of fistula repair breakdown and recurrence (Aim 1), identify predictors and characteristics of post-repair incontinence (Aim 2), supplemented by qualitative work among key stakeholders to identify feasible and acceptable strategies for modifying key risk factors of adverse outcomes (Aim 3). The three proposed specific aims address critical research gaps in the fistula literature and are expected to tangibly inform the development of clinical and counseling interventions to mitigate complications, improve post-surgical outcomes and quality of life. Our investigative approach seeks to elucidate which factors (e.g., patient and fistula characteristics, surgical factors, and post-repair behaviors and exposures) are most important in determining risk of post-surgical adverse outcome, thereby leading to appropriately targeted and contextually-adapted interventions, and will identify priority research areas needed for women with continued poor outcomes.

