Prior to fitting multivariable models, we will calculate the estimated correlation of all potential predictors to identify any highly correlated groups of predictors. We will not include such groups of predictors in any multivariable models. We will assess the adequacy of the proportional hazards assumption through inspection of Schoenfield residuals as a function of time. In the event our data violate the proportional hazards assumption, we will modify our modelling approach to accommodate interactions or stratification, as is most appropriate for the data. We will subsequently fit one multivariable proportional hazards regression model to document the comparative relationship between patient, fistula, fistula repair, and post-repair characteristics and the hazard rate of post-repair fistula breakdown and recurrence integrating all independent variables that were associated with the outcome in bivariable analyses at a conservative p threshold of p < 0.1. Final model selection will be determined via Akaike’s Information Criteria.^52^ Secondary analyses will assess time to post-repair fistula breakdown (< 3 months post-repair) and time to fistula recurrence (≥ 3 months post-repair) separately, and by fistula etiology (obstetric versus iatrogenic), although our study is not powered for secondary outcomes.

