To identify predictors and characteristics of post-repair incontinence (Aim 2), we will first estimate the proportion of women who experience post-repair incontinence and the 95% confidence interval at multiple time points (e.g., 6m, 12m, 2y and 3y). Our primary analysis of predictors of persistent post-repair incontinence will focus on incontinence at 3 months, the time point by which incontinence resolvable through surgery will have resolved per expert opinion. We will first estimate bivariable relationships between each predictor and post-repair incontinence at this time point using multi-level mixed effects logistic regression modeling procedures in Stata to accommodate the clustered nature of our data.^51^ Subsequently, we will estimate one multivariable model to understand the independent and joint effects of patient, fistula, fistula repair, and post-repair characteristics on post-repair incontinence at 3m, integrating all independent variables that were associated with the outcome in bivariable analyses at conservative p < 0.1 and addressing correlation as described for Aim 1. To identify predictors of incident post-repair incontinence, we will assess incident post-repair incontinence and factors associated with time to incident post-repair incontinence using the survival analysis methods described for Aim 1. Finally, we will conduct analyses of binary predictors of interest employing propensity scores and seek to develop classification rules following the methods described for Aim 1.

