**Predictor Variables**							
Patient-related: study participant characteristics, potentially important biological and social risk factors for poor health.							
Sociodemographics	Age, educational attainment	PQ	●				
	Income, assets, food security^58^	PQ	●				●
Obstetric history	Parity, pregnancy outcomes (prefistula, during-fistula), time since fistula development	PQ, MR	●				
Health status	Nutritional status^b^	MR	●	●	●	●	●
	Co-morbidities,^c^ urinary tract infection, functional health,^d^	PQ, MR	●	●	●	●	●
Fistula-related: selected characteristics illustrate fistula severity and physical burden of fistula.							
Fistula characteristics	Size, location, fistula etiology^e^, fistula type^f^, VVF grade^g^, vaginal scarring, bladder capacity, urethral length, bladder neck involvement, other urogyn diagnoses.	MR	●				
Fistula history	Time since fistula development, etiology, symptoms^h^, number of previous repairs, treatments.	PQ, MR	●				
Fistula repair-related: measures include provider training, procedural decisions, and complications.							
Repair procedure	Surgical route^i^; layers, suture type; anesthetic type; sling and tension; flap use, graft use and type, prophylactic antibiotic use, catheterization^j^	MR, PS	●				
Quality of care	Person-centered care	PQ	●				
Provider characteristics	Surgeon, surgical level and experience, repair center	PS	●				
Repair complications	Bleeding, infection, leakage, pain (48hrs+), catheter blockage, other	MR, PS	●				
Post-repair behaviors and exposures: variables capture physical and sexual risks.							
Physical activity and trauma	Moderate and vigorous activity, peak and long-term weight lifting^k^, physical violence^l^	PQ	●	●	●	●	●
Sexual activity and fertility	Post-surgical resumption of sexual activity, frequency of sexual activity, sexual satisfaction^m^, fertility intentions, menstruation, contraceptive use.	PQ	●	●	●	●	●
Lifestyle	Dietary quality, alcohol^n^, tobacco^o^, and caffeine consumption^p^; medical and traditional medical care.	PQ	●	●	●	●	●
Pregnancy-related factors: pregnancy-related factors below may contribute to risk of adverse outcomes through biological or social mechanisms.							
Pregnancy-related health	Chronic and pregnancy-related co-morbidities^q^, timing of pregnancy	PQ, MR	●	●	●	●	●
Antenatal care	ANC initiation, timing, frequency and location, birth planning	PQ, MR	●	●	●	●	●

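### As worded, the collinearity rule leaves whole correlated groups of predictors out of every multivariable model, so fistula severity could drop out of the adjusted analyses for both aims

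*Protocol article*

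**What the plan says.** All references are to the protocol article. Under Longitudinal cohort study, Data analysis, the Aim 1 text says that before multivariable modelling "we will calculate the estimated correlation of all potential predictors to identify any highly correlated groups of predictors". The next sentence is the rule at issue: "We will not include such groups of predictors in any multivariable models". What is excluded is the group, and the exclusion covers any multivariable model. No sentence retains a member of the group.

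The same paragraph then plans one multivariable model to "document the comparative relationship between patient, fistula, fistula repair, and post-repair characteristics", "integrating all independent variables that were associated with the outcome in bivariable analyses at a conservative p threshold of p < 0.1", with the final model chosen by AIC. The Aim 2 text builds its 3-month incontinence model in the same way, "addressing correlation as described for Aim 1".

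The Background treats severity features as known predictors. For recurrence, it cites a study in which "those with urethral involvement, damaged bladder neck, and presence of vaginal scarring had significantly higher incidence of fistula recurrence". For incontinence: "Predictors of immediate post-repair incontinence include fistula severity, including size and location, presence of vaginal scarring, and shorter urethral length". Table 1 collects size, location, type, grade, "vaginal scarring, bladder capacity, urethral length, bladder neck involvement" in one block meant to reflect severity. Footnote g lists two classification systems for grade.

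**The concern.** The usual remedy for collinearity is to keep one member of a correlated set, or to combine the members. Removing the whole set discards the shared information as well as the redundancy. Several measures of one construct are the likeliest to be flagged, and the severity block fits that description, with two gradings of the same fistula within it.

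Two things are at stake. First, repair-related predictors in Table 1, such as surgical route, flap use, surgeon level and catheter days, plausibly vary with severity, and post-repair behaviour may too. Without severity in the model, their adjusted effects could carry its effect. Second, the model is meant to compare fistula characteristics with the other domains, and it cannot do so for variables that the rule has removed.

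**Working it through.** The rule rests on no stated power, alpha or sample-size figure, so there is nothing of the plan's own to reproduce. The check has two parts: the text, then an illustration on assumed values.

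**1. The two rules side by side.** Take a severity variable that belongs to a flagged group and has bivariable p < 0.1. The correlation rule excludes it from any multivariable model, while the selection rule integrates it. The rules can be reconciled by order (correlation screen first, p-value screen on what is left), but then the exclusion takes full effect and the fistula domain may be thinly represented in the comparison.

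**2. How much would be removed.** The article gives no correlations and no cut-off. Assume five severity indicators with equal pairwise correlation ρ, n = 1000, and an indicator flagged when its correlation with at least one other reaches the cut-off. Mean number of the five removed over 300 simulated cohorts:

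| ρ | cut-off 0.5 | 0.6 | 0.7 | 0.8 |
|---|---|---|---|---|
| 0.3 | 0 | 0 | 0 | 0 |
| 0.5 | 4.19 | 0 | 0 | 0 |
| 0.6 | 5.0 | 4.1 | 0 | 0 |
| 0.7 | 5.0 | 5.0 | 4.05 | 0 |
| 0.8 | 5.0 | 5.0 | 5.0 | 3.96 |

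The result runs from nothing removed to everything removed, depending on two quantities that are not stated.

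**3. What removal could do.** Assumed model:
- Latent severity L is standard normal, and each of the five indicators is √ρ·L + √(1−ρ)·noise.
- A binary exposure equals 1 when g·L + noise > 0. The latent exposure–severity correlation is g/√(1+g²): 0.3/√1.09 = 0.29 for g = 0.3, and 0.6/√1.36 = 0.51 for g = 0.6.
- The hazard is 0.145·exp(b·L − b²/2) over one unit of follow-up. The severity hazard ratio per SD is exp(0.4) = 1.49 or exp(0.7) = 2.01. The event proportion is at most 1 − exp(−0.145) = 13.5%, a little below the article's figure of approximately 15%.
- The exposure's true hazard ratio is 1.0. Cox models without frailty were fitted in 150 cohorts per row.

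Mean hazard ratio for the exposure (share of runs with p < 0.05):

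| ρ | g | b | group dropped | one kept | all five kept |
|---|---|---|---|---|---|
| 0.6 | 0.3 | 0.4 | 1.19 (17%) | 1.07 (7%) | 1.02 (5%) |
| 0.6 | 0.3 | 0.7 | 1.35 (40%) | 1.12 (11%) | 1.02 (5%) |
| 0.6 | 0.6 | 0.4 | 1.38 (45%) | 1.16 (13%) | 1.05 (7%) |
| 0.6 | 0.6 | 0.7 | 1.71 (85%) | 1.26 (23%) | 1.06 (5%) |
| 0.8 | 0.3 | 0.4 | 1.20 (19%) | 1.04 (4%) | 1.02 (5%) |
| 0.8 | 0.3 | 0.7 | 1.35 (36%) | 1.05 (7%) | 1.01 (7%) |
| 0.8 | 0.6 | 0.4 | 1.41 (47%) | 1.09 (9%) | 1.03 (6%) |
| 0.8 | 0.6 | 0.7 | 1.75 (87%) | 1.16 (9%) | 1.05 (3%) |

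With 150 runs, the simulation standard error is √(0.05 × 0.95/150) = 1.8 percentage points near 5% and about 4 points near 45%. In every row, dropping the group gives the largest bias. Keeping one member removes most of it but not all.

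**The case against.** **The authors may have meant only that members of a group will not be entered together.** That is ordinary practice, and it fits the stated aim of comparing fistula characteristics with other domains. It is a plausible intention, but the sentence does not say it. Nor does it settle the matter: each aim has one multivariable model, so someone must choose which member enters, and the only selection tools stated (p < 0.1 and AIC) depend on the outcome.

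**A cut-off and the choice of representative belong in the full protocol or SAP.** Agreed, and their absence is not the point here. The point is a rule that the article does state.

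**A reader might infer that severity will be removed.** The documents do not support that. They report no correlations, never call the severity variables highly correlated, and set no cut-off. At ρ = 0.3 nothing is removed. Even when a group is flagged, severity variables outside it stay in.

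**A reader might also infer that severity features are the main known risk factors.** The Background does not go that far. For recurrence it also lists sexual activity, farm and heavy work, physical strain, walking and later childbirth, and it calls fistula characteristics likely to be important.

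**Other analyses still use severity.** This partly stands. Propensity-score analyses are planned for key modifiable factors (Aim 1) and for binary predictors of interest (Aim 2), and the correlation rule is not said to govern the exposure models. Severity also remains available to the bivariable analyses and classification rules. But under Aim 1 the propensity analyses are labelled secondary, their covariates are left to judgement, and none of these analyses gives severity's own adjusted effect.

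**Conclusion.** The concern holds as a defect in a stated rule. Taken literally, the plan excludes every highly correlated group from all multivariable models for both aims, against its own instruction to enter all variables with bivariable p < 0.1. The wording defect is clear from the text. Its practical size is not: severity could be lost wholly, partly or not at all.

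The simulated figures (1.19 to 1.75 with the group dropped, 1.04 to 1.26 with one member kept) show direction and plausible scale only. They rest on assumed severity effects, correlations and exposure links, on loss of all five indicators, and on a Cox model, so they say nothing numerical about the Aim 2 logistic model. They should not be read as forecasts for this cohort.

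The finding also does not establish that a severity measure must be forced into every model whatever its p-value. That is a separate and debatable choice of modelling strategy. The correction is still worth making before analysis, because the rule governs the main adjusted models and is easily repaired.

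**What to change.** Replace the exclusion sentence in the Aim 1 Data analysis text with:

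> Members of a highly correlated group will not be entered together. For each group we will retain one representative or a composite, chosen on clinical grounds without reference to the outcome (for example, one grading system for fistula severity). The other members will be swapped in as sensitivity analyses.

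Say that this applies to Aims 1 and 2; the Aim 2 cross-reference then carries the corrected rule. The correlation measure and cut-off can be set in the same place or in the SAP.

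One point for the choice: a composite may protect better than a single member. Under the assumed model with ρ = 0.6, one indicator shares 0.60 of its variance with severity, while the mean of five shares 5 × 0.6/(1 + 4 × 0.6) = 3/3.4 = 0.88.

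The cost is one sentence and slight extra analysis work for the sensitivity models, with no new data and no change to the design.

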#### Measures.

Primary predictors to be investigated include patient-related factors, fistula-related factors, fistula repair-related factors, and post-repair behaviors and exposures (Table 1), collected via structured questionnaire at all follow-up data collection points and from medical records and clinical forms when examinations are performed. Participant sociodemographic, fistula and fistula-repair characteristics will be measured at baseline, with questions on post-repair behaviors and exposures at each follow-up. Outcomes will be screened for at each data collection point; study interviewers will ask a series of questions on signs and symptoms to identify outcomes of interest, women who report new or changed urinary incontinence will be asked to return to the fistula repair facility for clinical exam to confirm fistula breakdown, recurrence, or incontinence. Women with persistent incontinence without fistula breakdown/recurrence will be asked to respond to a short supplemental questionnaire to characterize this incontinence. Women identified as pregnant will be asked to respond to a short supplemental questionnaire on pregnancy-related exposures and outcomes. We seek to develop a comprehensive longitudinal dataset capable of supporting broad inquiry into health and wellbeing following fistula repair.

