Other methods will also be used to better understand the contribution of risk factors of fistula repair breakdown and recurrence. To overcome the biases inherent to observational research in understanding causal effects,^46^ we propose conducting a series of secondary analyses employing propensity score methods.^47^ Propensity score methods account for systematic differences in baseline characteristics between exposed and unexposed participants, allowing for effects to be interpreted as causal, similar to a randomized experiment.^48,49^ Indeed, propensity score methods may reduce systematic differences between treatment groups compared to covariate adjustment methods.^47^ For these analyses, we will estimate a series of models for each key modifiable factor to be assessed, first developing models predicting the probability of the particular exposure using key baseline and other measures deemed to be relevant for developing the treatment weight, followed by analyses of the exposure and outcome incorporating the treatment weight to the methods described above. Finally, we will seek to construct a classification rule based on predictors using techniques such as recursive partitioning and random forests using routines in R to identify groups of women defined by the exposure characteristics that have high probability of experiencing the adverse outcome.^50^

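### Propensity weighting is said to give causal, trial-like effects for every key modifiable factor, though many arise or change after surgery and are recorded alongside the outcome with no stated time order

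*Protocol article*

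**What the plan says.** In the protocol article's Data analysis section, propensity score methods are brought in as secondary analyses for Aim 1, to deal with the biases of observational research. The stated property is: "Propensity score methods account for systematic differences in baseline characteristics between exposed and unexposed participants, allowing for effects to be interpreted as causal", and the sentence goes on to liken the result to a randomized experiment. The scope is wide: "we will estimate a series of models for each key modifiable factor to be assessed". The exposure model is built "using key baseline and other measures deemed to be relevant for developing the treatment weight", and the resulting treatment weight is carried into the survival models. Aim 2 repeats the approach for binary predictors.

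The Aim 2 primary analysis is a multilevel logistic model for the "joint effects of patient, fistula, fistula repair, and post-repair characteristics on post-repair incontinence at 3m".

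Under Measures and in Table 1, post-repair behaviours (activity and lifting, sexual activity, contraception, alcohol) and pregnancy-related factors are asked about at every contact, and outcomes are screened at every contact. Record-based predictors come "from medical records and clinical forms when examinations are performed". Study procedures makes the contacts from 6 weeks onward telephone calls. It also describes routine in-person clinical assessment at 6 weeks and 3 months, and symptom-triggered examinations across follow-up.

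The Discussion says the longitudinal design allows time-varying contributors to be evaluated. The Data analysis text does not take this up.

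**The concern.** Three separate problems sit behind one sentence.

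- **The claim itself.** Propensity weighting balances the covariates in the model and no others. Even perfect baseline balance says nothing about why one woman resumes sex or lifting at 2 months and another at 12, when recovery in between may drive both the behaviour and the outcome.
- **Reverse causation.** A woman who starts to leak may stop having sex or lifting. If the behaviour reported at the contact where leakage is found is taken as the exposure, stopping looks like a cause. The Background shows how this can arise: "A study in Guinea reported that women not sexually active at follow-up" had higher recurrence, while intercourse was named as a precursor by 10% of women in the same study.
- **Time zero.** A woman whose repair breaks down early has little time to become exposed. If she is labelled unexposed from surgery, early events collect in the unexposed group.

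Aim 3 builds intervention concepts on the risk factors found in Aims 1 and 2. A behaviour that looks protective only because of time order would point the counselling work the wrong way.

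**Working it through.** The plan gives no figure for this point, so there is none to reproduce. The check is of the text first, and then of how large the bias could be.

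**1. Text side by side (protocol article).**

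| Element | What is stated | Where |
|---|---|---|
| What is balanced | Baseline characteristics, in the general description | Data analysis |
| Covariates in the weight | Baseline and other measures; timing relative to exposure not given | Data analysis |
| Exposures covered | Each key modifiable factor | Data analysis |
| When behaviours are measured | Each follow-up; many at baseline too | Measures; Table 1 |
| When outcomes are screened | The same contacts | Measures |
| Order of exposure and outcome | Not stated | Data analysis, Aims 1 and 2 |
| Coding of post-repair exposures | Not stated | Data analysis |

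On coding, the text points both ways. Sample size uses a two-sample log-rank comparison and expressly includes post-repair behaviours; that test in its standard form compares groups fixed at time zero. Aim 2 speaks of binary predictors. Against this, the Discussion speaks of time-varying contributors.

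**2. Reverse causation.** Assume 60% of women without leakage report the behaviour, no true effect, and that leakage cuts reporting by a fraction f. Then q = 0.60 × (1 − f), and the apparent OR = [q/(1 − q)] / [0.60/0.40].

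- f = 0.25: q = 0.45; 0.818/1.5 = 0.55
- f = 0.50: q = 0.30; 0.429/1.5 = 0.29
- f = 0.75: q = 0.15; 0.176/1.5 = 0.12

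The 60% and the values of f are assumptions.

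**3. Immortal time, only if coding is ever/never from surgery.** From the article: 15% events (Sample size), 36 months of follow-up, and events mostly in the first 12 months (Background). Cumulative hazard = −ln(0.85) = 0.163. The exposure has no effect and starts at 1.5 months plus an exponential delay (assumed).

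Ever/never ratio = (events/person-time in women exposed before event or month 36) / (the same in the rest), with all time counted from surgery.

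| Median delay (months), all women start eventually | Constant hazard | 80% of hazard in year 1 (assumed) |
|---|---|---|
| 3 | 0.02 | 0.01 |
| 6 | 0.07 | 0.03 |
| 12 | 0.20 | 0.08 |
| 24 | 0.32 | 0.14 |

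A milder set assumes that only 30%, 50% or 70% of women ever start, with mean delays of 3, 6 or 12 months and 60% of the hazard in year 1. The ratios are about 0.3 to 0.7, and about 0.5 for 50% and 6 months.

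Moving person-time before the start of exposure to the unexposed side gives 0.99 to 1.01 throughout, provided the comparison is made within periods of follow-up. With front-loaded hazard and no such stratification the crude ratio is still 0.34 to 0.43. A Cox model compares women at the same follow-up time and so avoids this. Covariate weighting does not correct misallocated person-time.

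**4. Record-based exposures.** Table 1 lists BMI and anemia from medical records at every contact to 36 months. Routine in-person assessment is described only to 3 months. After that the contacts are telephone calls and examinations are prompted by symptoms, so later values will exist mainly for women with a suspected outcome.

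**The case against.** A reader might infer that the plan commits to a single baseline propensity score with ever/never coding, and so certainly has immortal-time bias. The documents do not support that. The exposure model uses other measures as well as baseline ones, and the sentence on baseline characteristics can be read as a general account of the method. Ever/never coding from surgery is nowhere stated, and the Discussion leans towards time-varying evaluation. The ratios in step 3 therefore illustrate a possible error; they do not measure this plan.

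It is also fair that coding, lags and weight construction are often left to a fuller protocol or analysis plan, so their absence alone is no finding. Several behaviours are also recorded at baseline, and repair-related factors such as antibiotics or flap use are recorded then only; a single score suits those. The propensity analyses are secondary, and Aim 3 also draws on the literature and expert experience. The result on women not sexually active comes from another study, and reading it as reverse causation is plausible but cannot be checked here.

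That does not rescue the stated property. No fuller document makes "allowing for effects to be interpreted as causal, similar to a randomized experiment" true of weighting on measured covariates, least of all for behaviours that change after surgery. The 3-month incontinence model is a primary analysis, and the shared timing of exposure and outcome is part of the stated design.

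**Conclusion.** The concern holds in limited form.

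- **Firm:** the causal, trial-like claim is wrong as written. Behaviours and outcomes come from the same contacts without a stated order, so reverse causation is a real risk in the propensity analyses and in the primary 3-month model.
- **Conditional:** immortal-time bias arises only if post-repair factors are coded as fixed groups from surgery. Its direction would then be clear, with a null behaviour looking protective. Its size, from about 0.01 to 0.7 for a true 1.0, rests on assumed start times, exposure shares and event timing.
- **Limited:** outcome-dependent recording of BMI and anemia is a concern mainly after 3 months.

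This should be fixed. It is not a fatal flaw, because the propensity analyses are secondary and the data needed are already being collected.

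**What to change.** 1. Remove or qualify the causal sentence so that it claims control of measured confounding only, and add a sensitivity analysis for unmeasured confounding (for example E-values).
2. For factors that arise or change after surgery, use time-updated exposures lagged to the last contact before symptom onset, with time-varying weights in a marginal structural Cox model, or landmark analyses. Keep single propensity scores for factors fixed at surgery.
3. In the 3-month incontinence model, use only exposures recorded before the 3-month contact, and adjust for or stratify by leakage already present when the exposure was recorded. Timing alone reduces reverse causation but does not remove it, since women may already leak at 2 or 6 weeks.
4. For record-based exposures such as BMI and anemia, use baseline, 2-week and routine 6-week and 3-month values, lagged before the outcome. Do not use later values obtained only at symptom-triggered visits.

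The cost is analysis-plan wording, more programming and wider intervals from lagging and weighting. No new data collection is needed.
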